### Design

An observational, prospective, and multicentre study will be carried out with the participation of 9 public hospitals of the Spanish National Health System, located in 7 Autonomous Communities (Andalusia, Aragon, Catalonia, Valencia, Canary Islands, Murcia, and Navarre). The study will be carried out between 01/09/2022 and 31/12/2024.

### Sample/Participants

The study population consists of the users of the medical and surgical inpatient units of the participating hospitals. Participants will be selected through consecutive case sampling.

The study will include patients aged 65 years or older who are admitted to the inpatient units, with an expected stay of at least 48h and who sign the informed consent form (or their legal guardian). Patients admitted with enteral nutrition or parenteral nutrition, terminally ill patients, patients with a primary diagnosis of cancer, patients admitted to critical care units, and with a diagnosis of COVID-19 illness at admission or during the stay will be excluded. Withdrawal criteria during follow-up will include: i) patients transferred to another hospital or unit not participating in the study; ii) any patient meeting any exclusion criteria at any time.

To calculate the sample size, the Freeman criterion for multivariate logistic regression analysis in epidemiological studies was considered first [23]. Taking into account that a maximum of 20 independent variables (k) will be included in the model at the same time and that it is intended to carry out both a global analysis and an analysis by a hospital, an initial sample size of n = 10*(k+1) = 10*(20+1) = 210 patients per hospital is estimated and, estimating possible losses of 15%, a total of 242 patients per hospital will be necessary. Secondly, given that we intend to study the prevalence of malnutrition and/or dysphagia in each of the participating hospitals and that in the literature the prevalence of malnutrition and/or dysphagia presents great variability, it seems appropriate to consider a prevalence of 50% (will guarantee the necessary sample size) which, for the confidence of 95%, a precision of 5% and a percentage of losses of 15%, will require a sample size per hospital of 453 patients (GRANMO-IMIM sample size calculator). Therefore, the total sample will be 4077 participants, and a recruitment and follow-up period of 18 months is estimated to be necessary.

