### Aims

The main objective of this project is to assess the risk of malnutrition and nutritional status on admission and its evolution until discharge, in patients aged 65 and over admitted to medical and surgical units in hospitals of the Spanish National Health System. In addition, the aim is to respond to the following specific objectives:

To identify the incidence and prevalence of risk of malnutrition and the presence of malnutrition and associated factors on patient admission and discharge.To describe the evolution of nutritional status during patient hospitalization.To analyze the average length of stay, hospital mortality, and early readmission as a function of nutritional status at admission and the presence of dysphagia in the study cohort.To determine the incidence and prevalence of dysphagia and associated factors on admission and discharge.To determine satisfaction with the quality of patient nutrition at discharge, the type of hospital food service, and the characteristics of the hospital nutrition unit.

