### Variables and instruments

The study variables are organized into eight groups: i) Nutritional status; ii) Dysphagia; iii) Food quality and environment; iv) Socio-demographic variables; v) Clinical, functional, cognitive, and frailty variables; vi) Variables related to the risk profile; vii) Context variables; viii) Variables related to the care process.

Specifically, nutritional status and dysphagia are considered the main variables of the study. Likewise, the variables related to nutritional status are organized into:

Risk of malnutrition on admission: Malnutrition Universal Screening Tool (MUST) will be used to determine the risk of malnutrition. This questionnaire will measure current weight (kg), estimated weight three months ago (kg), height (cm), and Body Mass Index (BMI) (kg/m2). If height and weight cannot be measured or obtained, they will be estimated mid-upper arm circumference (MUAC) and calf circumference (CC) are set for weight and forearm length for height by the nutrition staff of each hospital. All patients included in the study will be assessed on admission, every 7 days, and at discharge.Diagnosis of malnutrition and degree of severity at admission: Global Leadership Initiative on Malnutrition (GLIM) criteria will be used for the population identified as high risk according to MUST. In addition, the following biochemical parameters will be collected: albumin, prealbumin CRP, CRP/prealbumin ratio, transferrin, total cholesterol, and the total number of lymphocytes. They will be collected on admission, every 7 days, and discharge provided that the minimum time for their re-determination has elapsed.Type of nutritional care established (according to risk and diagnosis of malnutrition): Includes aspects such as referral to the nutrition and dietetics unit, dietary adaptation according to alteration, nutritional supplementation, type of nutrition, or nutritional education. It will be recorded within 48 hours of admission, every 7 days and at discharge, and in case of any modification in the selected intervention, the starting date should be noted.Daily intake: a semi-quantitative questionnaire will be used to record the amount of intake made during the days of admission.

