Additionally, multilevel models (generalized linear mixed models) with multivariate logistic link function will be implemented to account for possible correlation between patients admitted to the same medical or surgical units (first level) or hospital (second level).

In case of losses to follow-up, multiple imputation techniques will be used for missing data. In all cases, bilateral contrast will be used and will be considered significant when p<0.05. The analysis will be performed using SPSS v28.

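### Withdrawing patients who become terminally ill or move to critical care during the stay biases hospital mortality and in-stay incidence downward if they are at higher risk than those who remain

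*Protocol article*

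**What the plan says.** All references are to the protocol article.

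- **Exclusion criteria (Sample/Participants).** The list includes "Patients admitted with enteral nutrition or parenteral nutrition, terminally ill patients, patients with a primary diagnosis of cancer, patients admitted to critical care units", and it continues with patients "with a diagnosis of COVID-19 illness at admission or during the stay will be excluded".
- **Withdrawal criteria during follow-up (same section).** Rule (i) covers "patients transferred to another hospital or unit not participating in the study". Rule (ii) covers "any patient meeting any exclusion criteria at any time".
- **Outcomes.** The research hypothesis is that nutritional status worsens up to discharge and may raise stay, mortality and readmission. One specific objective analyses length of stay, "hospital mortality, and early readmission as a function of nutritional status at admission and the presence of dysphagia in the study cohort". Data analysis adds incidence of malnutrition risk, undernutrition and dysphagia up to discharge, with Cox models for mortality and time to readmission.
- **Missing data (Data analysis).** "In case of losses to follow-up, multiple imputation techniques will be used for missing data".
- **Care recorded during the stay (Variables and instruments).** The items include "nutritional supplementation, type of nutrition, or nutritional education", recorded within 48 hours of admission, every 7 days and at discharge.

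Nothing in the article says that withdrawn patients are still followed for discharge or vital status. The limitations section does not mention bias from withdrawal.

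**The concern.** Criteria that properly define who enters the study are reused to remove patients after entry. Terminal status and critical care transfer during the stay often lie on the path to death or to a worse nutritional course, which are what the study measures. A patient who becomes terminally ill on the ward is withdrawn before dying, so the death does not reach the mortality analysis. Rule (i) has the same effect for critical care: the study runs in medical and surgical units and excludes critical care patients, so a move there is a move to a non-participating unit.

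At stake are the absolute estimates of hospital mortality and in-stay incidence, and the associations of outcome with nutritional status. In the Cox models, censoring at such a withdrawal would be informative. Those models also use change in nutritional status up to discharge, which a withdrawn patient lacks.

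**Working it through.** **1. The plan's own figure.** With 50% prevalence, 95% confidence and precision of 5 points, n = 1.96² × 0.5 × 0.5 / 0.05² = 384.15, rounded up to 385. With 15% losses, 385 / 0.85 = 452.9, rounded up to 453, and 453 × 9 = 4077. The stated numbers reproduce. They rest on the precision of a prevalence and do not depend on the withdrawal rule.

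**2. Mortality and its association with malnutrition.** The article gives no withdrawal rates and no mortality rates, so these inputs are assumed: mortality r of 8% in malnourished and 4% in other patients (true RR 2.0), with 27% malnourished (the Introduction cites 26.9% on admission). True overall mortality is 0.27 × 8% + 0.73 × 4% = 5.1%. Let w be the share of deaths preceded by withdrawal. If those patients drop out of numerator and denominator, observed risk = r(1 − w) / (1 − rw).

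| w, malnourished / others | Observed risk, malnourished | Observed risk, others | Observed RR | Observed overall |
|---|---|---|---|---|
| 60% / 40% | 0.032/0.952 = 3.36% | 0.024/0.984 = 2.44% | 1.38 | 2.7% |
| 50% / 50% | 0.040/0.960 = 4.17% | 0.020/0.980 = 2.04% | 2.04 | 2.6% |
| 40% / 60% | 0.048/0.968 = 4.96% | 0.016/0.976 = 1.64% | about 3.0 | 2.5% |

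Overall for the first row: (0.27 × 0.032 + 0.73 × 0.024) / (0.27 × 0.952 + 0.73 × 0.984) = 0.02616 / 0.97536 = 2.7%. The other rows follow in the same way. Overall mortality falls in every row, whereas the RR moves in either direction. The formula removes only patients who die; withdrawn survivors would change the figures somewhat.

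**3. Check with a different model that includes withdrawn survivors.** Let w now be the fraction of all patients withdrawn, m their mortality and M the complete-cohort mortality. Observed mortality = (M − wm) / (1 − w). With assumed M = 5%, w = 5% and m = 30%: (0.05 − 0.015) / 0.95 = 3.7%, a relative bias of −26%. Over w of 2% to 10% and m of 20% to 40%, the relative bias runs from −6% to −78%.

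For the association, assume mortality among those who stay of 5% and 2.5% (observed RR 2.0) and 30% among the withdrawn:

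- 5% withdrawn in both groups: complete-cohort RR = (0.95 × 0.05 + 0.05 × 0.30) / (0.95 × 0.025 + 0.05 × 0.30) = 0.0625 / 0.03875 = 1.61.
- 15% against 5% withdrawn: (0.85 × 0.05 + 0.15 × 0.30) / 0.03875 = 0.0875 / 0.03875 = 2.26.

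The observed 2.0 is too high in one case and too low in the other.

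**4. In-stay incidence.** Take 18% as the complete-cohort value (the Introduction cites it for malnutrition developing in hospital). If the withdrawn have k times the incidence of those who stay, observed incidence = 18% / ((1 − w) + wk).

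| Withdrawn (assumed) | k = 1.5 | k = 3 |
|---|---|---|
| 5% | 17.6% | 16.4% |
| 10% | 17.1% | 15.0% |
| 15% | 16.7% | 13.9% |

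The relative bias runs from −2% to −23%. It is zero only if the withdrawn have the same risk as those who stay.

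**The case against.** The strongest reply has four parts.

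- **The main objective largely survives.** Malnutrition risk and nutritional status on admission are untouched by later withdrawal, provided baseline data are kept, and the sample size is unaffected. This stands. Evolution to discharge, incidence, stay and mortality remain exposed.
- **Imputation may help.** Screening scores, biochemistry, function, comorbidity and weekly data exist before withdrawal, and could reduce bias in discharge nutritional status if data are missing at random given them. This also stands in part. However, the article ties imputation to losses to follow-up and does not say that it covers withdrawal by rule. Missingness at random is doubtful when the reason for missingness is deterioration.
- **Some of this is a choice of population.** The in-stay COVID-19 exclusion is explicit, and neither COVID-19 nor a new cancer diagnosis is in itself nutritional deterioration. That is fair, and the point rests on terminal status and critical care.
- **The article is condensed and its flowcharts are not shown.** The full protocol may retain data up to withdrawal. That limits certainty about what will be done. The rule itself is stated outright.

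Three stronger readings are tempting but not supported. A reader might infer that starting enteral or parenteral nutrition during the stay triggers withdrawal, but that exclusion is worded as a condition at admission, and type of nutrition is followed weekly; the wording is ambiguous at most. A reader might infer that values would be imputed only from patients who did not deteriorate, but those who worsen on the ward without meeting a criterion remain. A reader might infer that the association with malnutrition must be attenuated. That would require more withdrawal of malnourished patients, for which the article gives no figure, and the calculations show movement both ways.

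**Conclusion.** The concern holds for patients who become terminally ill or go to critical care during the stay. Rules (i) and (ii) remove them before the outcomes are observed. If their risk exceeds that of patients who remain, absolute hospital mortality and in-stay incidence are biased downward. The direction of bias in associations with nutritional status is unknown.

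The size cannot be derived from the article. The fall in mortality from 5.1% to 2.7%, the observed RR of 1.38 or about 3.0 against a true 2.0, and the incidence range in the working all rest on assumed mortality and withdrawal rates. They show that the effect can be material, not what it will be.

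**What to change.** - Apply the exclusion criteria for cohort membership at admission only. Delete rule (ii), and delete the reference to a unit in rule (i); otherwise a critical care transfer would still end follow-up.
- Keep all enrolled patients in the analysis cohort. Record the dates of critical care transfer, terminal status and in-stay COVID-19, and take length of stay, vital status and readmission from the hospital record.
- Treat these events as intercurrent or competing events in the analysis. Report them, and any remaining withdrawals, by reason and baseline nutritional status, with a sensitivity analysis.
- If the in-stay COVID-19 exclusion is kept as a choice of population, report results with and without those patients.
- Reconcile the enteral and parenteral nutrition exclusion and rule (ii) in Sample/Participants with the weekly recording of type of nutrition in Variables and instruments.

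The cost is protocol wording and a few dated REDCap fields, with no added patients. Some weekly assessments will be missing while a patient is off the ward. If data collection has ended, stay and vital status may still be retrievable from hospital records, subject to consent and approvals.

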In Spain, the prevalence of undernutrition in people over 65 years of age is around 10%, with a risk prevalence of 23.3% [12]. In the hospital setting, the PREDYCES (Prevalence and costs of malnutrition in hospitalized patients) study established a prevalence of disease-related undernutrition of 23.7% in the general population, increasing to 37% in patients over 70 years of age [5]. Recent studies establish a prevalence of disease-related malnutrition on admission to inpatient units of 26.9% and, in addition, 18% of patients develop malnutrition during hospital stay [13]. Some authors point to an under-diagnosis of this problem, possibly related to the lack of standards in the detection and screening of malnutrition risk [13]. For these reasons, it is estimated that at least one in three patients over 65 years of age admitted to the hospital is malnourished, with an additional cost of between €1,400–1,800 for each hospital admission of a patient at risk of disease-related malnutrition [5,14].

On the other hand, oropharyngeal dysphagia is defined as the difficulty or inability to swallow solid, semi-solid, or liquid food from the oral cavity to the stomach [3]. Dysphagia is a symptom that accompanies other diseases and can affect up to 30–40% of the population over 65 years of age and up to 44% of elderly people admitted to hospital. It is estimated that, in Europe, 80% of patients are neither diagnosed nor receive any treatment for this pathology [15]. Furthermore, dysphagia is associated with a higher prevalence of malnutrition, along with other conditions such as frailty [16], neurological diseases, or neoplasms [17]. Some studies establish a joint prevalence of undernutrition and dysphagia ranging from 3–29% [18]. However, no international studies addressing both problems together in the hospital setting were retrieved.

Some factors that may explain the high rates of disease-related malnutrition and dysphagia are the lack of means and the scarcity of information on nutrition by professionals [13], as well as the quality of the food offered in hospitals [19]. The level of acceptance of hospital food has an important relationship with the user’s overall satisfaction and quality of life during admission [20]. Thus, the assessment of the quality of menus during hospital admission and patient satisfaction is considered an appropriate method of nutritional assessment in patients at risk of malnutrition and dysphagia [21].

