### Data analysis

A descriptive analysis of all the study variables will be carried out, using the appropriate measures according to the type of variable and their corresponding 95% CIs. Firstly, depending on the groups to be compared and compliance with the application requirements, a bivariate analysis will be performed, including the chi-squared or Fisher’s exact test (qualitative variables) and Student’s t-test, ANOVA, Mann-Whitney U-test, or Kruskal-Wallis (quantitative variables), depending on the application conditions.

For the analysis of the evolution of the risk of malnutrition, McNemar’s test or Cochran’s Q test will be used for qualitative variables and paired t-test or Friedman’s rank test for quantitative variables. The incidence of risk of malnutrition and undernutrition will be calculated, as for dysphagia, during the care process and at patient discharge, estimating their corresponding Odds Ratios and 95% CI using logistic regression models.

To assess the possible risk factors for both malnutrition and dysphagia and the socio-demographic and clinical characteristics of the patients, multivariate logistic regression models will be constructed. As independent variables will include: type of nutritional care established according to the risk of malnutrition; daily intake; suspected and diagnosed dysphagia and days of stay. As control variables will include: those related to the risk profile; sociodemographic (sex, age); clinical, functional, cognitive and frailty variables. In the case of mortality and time to readmission, multivariate Cox regression models will be fitted. Independent variables will be included: level of risk of malnutrition at admission; diagnosis of malnutrition at admission; change in risk of malnutrition at admission, at 7 days and at discharge; change in nutritional status at admission, at 7 days and at discharge. Control variables will include: type of nutritional care established (according to risk of malnutrition); daily intake; contextual; related to risk profile; sociodemographic; clinical, functional, cognitive and frailty variables; suspected and diagnosed dysphagia. In all multivariate models, possible interaction effects and possible collinearity will be analyzed.

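### The patients-per-variable rule ignores the event share, so it does not show that a logistic model with up to 20 variables can be supported in each hospital

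*Protocol article*

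**What the plan says.** The Sample/Participants section makes two calculations.

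The first concerns regression. It states that "the Freeman criterion for multivariate logistic regression analysis in epidemiological studies was considered first". The model may hold up to 20 variables at once. On the level of analysis, the section says: "it is intended to carry out both a global analysis and an analysis by a hospital". From these premises it derives "n = 10*(k+1) = 10*(20+1) = 210 patients per hospital is estimated". An allowance of 15% for losses then raises the figure to 242.

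The second concerns the precision of a prevalence in each hospital: 50% prevalence, 95% confidence, 5% precision and 15% losses. It gives 453 per hospital. The study adopts this figure, for a total of 4077 over nine hospitals.

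The Data analysis section plans multivariate logistic models for malnutrition and dysphagia and adds: "In all multivariate models, possible interaction effects and possible collinearity will be analyzed". It also plans generalised linear mixed models with unit and hospital as levels. The Introduction supplies the event shares used below, including the statement that "in addition, 18% of patients develop malnutrition during hospital stay".

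**The concern.** In a logistic model the information is limited by the smaller of the two outcome groups, not by the total number of patients. A rule of ten patients per variable gives the same answer whether the outcome occurs in 5% or in 50% of patients. It therefore cannot show that 20 variables are supportable for a given outcome. The precision calculation that sets the final size does not fill the gap, because it addresses the width of a confidence interval for one proportion.

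At stake are the hospital-level risk-factor models. With few events per variable, adjusted odds ratios tend to be unstable and too far from 1, with unreliable intervals. Across nine hospitals, that noise could be read as real differences between centres. Incident malnutrition is the most exposed outcome, and the incidence of malnutrition with its associated factors is among the specific objectives.

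**Working it through.** **Reproducing the plan's figures**
- Regression rule: 10 × (20 + 1) = 210. Losses: 210 × 1.15 = 241.5, so 242. Both reproduce.
- Precision: 1.96² × 0.5 × 0.5 / 0.05² = 384.1, so 385 evaluable. Losses: 385 / 0.85 = 452.9, so 453. Total: 9 × 453 = 4077. All reproduce.

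**Inputs for the check**
- Evaluable patients per hospital: 385 (453 less 15%). The no-loss case is 453. Pooled evaluable: 9 × 385 = 3465.
- Variables: 20, the stated maximum.
- Event shares from the Introduction: undernutrition 23.7% in inpatients overall and 37% over age 70; malnutrition on admission 26.9%; development of malnutrition during the stay 18%; dysphagia in older inpatients up to 44%. The 50% is the planning value in Sample/Participants.
- The Introduction does not say whether the 18% refers to all patients or only to those free of malnutrition on admission, so both are shown. The second uses 1 − 0.269 = 0.731.

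**Formula:** events per variable = n × event share / 20.

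| Outcome and share | Events at 385 | Per variable at 385 | Per variable at 453 |
|---|---|---|---|
| Undernutrition, 23.7% | 91.2 | 4.6 | 5.4 |
| Malnutrition on admission, 26.9% | 103.6 | 5.2 | 6.1 |
| Undernutrition over 70, 37% | 142.45 | 7.1 | 8.4 |
| Dysphagia, 44% | 169.4 | 8.5 | 10.0 |
| Planning value, 50% | 192.5 | 9.6 | 11.3 |
| Incident malnutrition, 18% of all | 69.3 | 3.5 | 4.1 |
| Incident malnutrition, 18% of those at risk | 50.7 | 2.5 | 3.0 |

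The smaller outcome group cannot exceed half the patients, so 9.6 is the ceiling for any binary outcome at 385 evaluable.

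**Pooled data (3465)**
- Malnutrition on admission: 3465 × 0.269 = 932 events, 932 / 20 = 46.6 per variable.
- Incident malnutrition: 3465 × 0.18 = 624 events, 31.2 per variable; or 3465 × 0.731 × 0.18 = 456 events, 22.8 per variable.

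**What ten events per variable would need in one hospital:** 200 / 0.269 = 743.5, so 744 evaluable, and 744 / 0.85 = 875.3, so 876 recruited, against the planned 453.

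**Parameters against variables.** The table counts each variable once. Type of nutritional care, as described under Variables and instruments, has several categories, and interactions are to be examined in all multivariate models. Each extra category or product term uses a further parameter, so events per parameter are lower than the table shows.

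**The case against.** The strongest case on the other side has five parts.

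- **The document never promises ten events per variable.** It applies a named patient-count criterion and does so consistently. This stands. Ten is a conventional benchmark brought in here, so the point is about the choice of rule and not a contradiction in the text.
- **210 does not govern the study.** This also stands. A reader might infer that hospital models will run on 210 patients, but the section goes on to adopt 453. The check above therefore uses 385 and 453 only.
- **The low shares are not the whole picture.** A reader might infer that every hospital model has only about 2.5 to 5 events per variable. The documents do not support that: at 385, the 37%, 44% and 50% shares give 7.1, 8.5 and 9.6. Admission measures are also taken in the first 24–48 hours, so later losses need not remove them. At 453, dysphagia at 44% reaches about 10 and the 50% value reaches 11.3. Malnutrition stays below 10 at 453 for its cited shares of 18% to 37%.
- **Twenty is a maximum, and the Data analysis section specifies no separate hospital regressions.** It already plans multilevel models with hospital as a level. This tempers the point but does not remove it: the sizing sentence itself links the 20 variables to a by-hospital analysis and states the result per hospital.
- **Harm is not certain.** With roughly 100 to 190 events per hospital for many prevalent outcomes, separation and serious bias cannot be taken for granted. The fair description is a risk.

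The two loss adjustments also differ: 210 × 1.15 = 242, whereas the method behind 453 would give 210 / 0.85 = 247.1, so 248. A reader might take this as a sizing error that matters. It has no effect, because 453 exceeds both, and it is an editorial note only.

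**Conclusion.** The concern holds for hospital-level models. The regression part of the sample size justification ignores the event share and so does not support 20 variables in each hospital. At 385 evaluable patients, events per variable are about 4.6 to 8.5 for prevalent outcomes at the cited shares, 9.6 at the planning value, and 2.5 to 3.5 for incident malnutrition. With no losses, the prevalent outcomes range from 5.4 to 11.3. Models with all 20 variables are at material risk of overfitting for malnutrition, most of all for incident malnutrition. The shortfall is mild for dysphagia at 44% and for any outcome near 50%.

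The pooled malnutrition models are adequate (about 23 to 47 events per variable), and the precision basis for 453 per hospital reproduces and is unaffected.

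The conclusion assumes that the shares in the Introduction carry over to this cohort, that all 20 variables are used at once, that losses are the planned 15% (or nil, as shown), and that about ten events per variable is a sensible yardstick.

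**What to change.** Keep n = 4077 and change the text as follows.

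1. State that models with up to 20 variables are fitted to the pooled data.
2. Examine differences between hospitals through hospital-by-factor terms or random slopes in the multilevel models already planned in the Data analysis section. With nine hospitals, slope variances will be imprecise, so restrict this to a few factors named in advance.
3. By hospital, report prevalence and incidence with confidence intervals, which is what the 453 was sized for.
4. If any hospital-level regression is kept, set its number of parameters from the expected events. At one parameter per ten events, 50.7 to 103.6 events allow about 5 to 10 for malnutrition. Alternatively, use penalised estimation, after checking that the named software offers it.
5. Restate the regression part of the justification in events per parameter, counting categories and interaction terms.
6. As an editorial matter, use one loss convention for both calculations.

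This needs no extra patients and no new data. The cost is that fully adjusted hospital-specific models are no longer offered.
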